## Abstract

Supplemental Digital Content is available in the text

## Introduction

1

Congenital auricular deformities (CAD) or congenital ear malformation are common in children. However, the prevalence of CAD is varied surprisingly from 1.7% to 50% among different populations,^[1–5]^ which may at least partially due to definition and diagnosis criteria. CAD will not only affect the appearance, but also hearing and mental health of the child. Parents’ mental health and quality of life may also be affected. Observational study has shown that about 70% infants with CAD at birth will recover naturally at 1 years old, but who will recover spontaneously is unclear.^[3]^

Traditional treatments for CAD are mainly surgical, which normally be arranged at around 6 years old.^[6]^ They are invasive and painful by its nature, and complications are not rare,^[7]^ including hematoma, infection, bleeding, allergic reactions, and necrosis, hypertrophic scars, keloids, fistulae, and recurrence.^[8]^ What is more, impairment of hearing or mental health of the child affected may already happened, which may have life-long consequences.^[9,10]^ Additionally, surgeries and subsequent care are expensive, bringing considerable economic burden to the family and society.

Non-surgical interventions of CAD were initialized in the 1980s.^[11]^ They are attractive for many health professionals and patients for the noninvasive nature, relatively easy process, sound curative rate and low cost compared with surgeries. At the primitive stage, doctors used tape and stick to shape the ear of children with CAD and found promising results, but highly relied on the skills of the doctors.^[12,13]^ Tape and stick were evolved to ear molding which increased the standardization of the treatment in recent decade.^[14]^ Studies found that the effectiveness rate of ear molding for CAD was up to 90%, and earlier intervention could lead to better outcomes, with few adverse events.^[15–19]^ However, these studies are mainly observational study or noncontrolled study, fall short of methodological rigour and prone to biases. As far as we know, there has been no randomized controlled trial (RCT) evaluating the effectiveness, safety and cost-effectiveness of ear molding for CAD and.

## Objective

2

The objective of this study is to evaluate the effectiveness, safety and cost-effectiveness of ear molding for CAD.

## Methods

3

### Study design and setting

3.1

A multicenter, assessor-blind, parallel 2 arms RCT will compare ear molding with waiting list in children with CAD who are in attendance in 8 woman and child hospitals in cities including Chengdu, Chongqing, Zhengzhou in China. The study has been submitted to the Ethnic Committee of Medical Research of West China Medical Centre, Sichuan University (K2020016) and was registered in the Chinese Clinical Trial Registry (ChiCTR2000031052) 21 March 2020.

The protocol is in accordance with the 2013 SPIRIT (standard protocol items: Recommendations for Interventional Trials) statement.^[20,21]^ The procedure of the trial is presented in Table 1.

**Table 1 T1:**
[figure not shown]
Process of the trial.

### Participants

3.2

#### Inclusion criteria

3.2.1

The inclusion criteria recommended by the expert consensus on the ear molding for congenital auricular deformation made by the Subspecialty Group of Pediatrics, Society of Otorhinolaryngology Head and Neck Surgery, Chinese Medical Association was adopted.^[22]^ The inclusion criteria are:

(1)Children aged 0 to 3 days,(2)Diagnosis of auricle morphological abnormalities, including: prominent ear, Stahl's ear, top ear, cup ear, cryptotia, abnormal convex ear nails Conchal crus, helical rim deformity, mixed ear deformities combining 2 or more deformities, and other auricle distortions;(3)Diagnosis of Microtia Marx classification I degree.^[23]^

#### Exclusion criteria

3.2.2

(1)Low birth weight infants (weighing less than 2500 g),(2)with multiple organ deformities,(3)Acute dermatitis,(4)Patients with other health-related reasons that are not suitable for participation in the study.

### Recruitment

3.3

Children born at the Department of Obstetrics of participant hospitals will be examined by health professionals against CAD within 3 days in the department. Parents of children diagnosed with CAD and eligible for the inclusion and exclusion criteria will be invited to participate into the trial. Children whose parents signed the informed consent form will be included in the study.

### Randomization and allocation concealment

3.4

A biostatistician will generate the random sequence using computer program. Central randomization will be performed by the biostatistician to achieve allocation concealment. Each study center will recruit participants according to the inclusion and exclusion criteria and obtain the informed consent from participants’ parents. After completing the demographic data collection, baseline assessment and baseline data entry, study center will contact the biostatisticians to obtain a grouping code to randomly assign the participant to either the intervention or the control group.

### Intervention

3.5

Participants in the intervention group will receive ear molding delivered by health professionals within 3 days of birth besides usual neonatal care, with a treatment duration of 2 weeks and followed up until 6 weeks from the start of the treatment.

### Control

3.6

The control group will be waiting list and receive usual neonatal care. Participants will be followed up at the same intervals as the intervention group until the sixth week after birth. After that, participants will be offered ear molding treatment as the same as the intervention group according to parents’ will, if the participant is not recovered spontaneously.

### Treatment monitoring and discontinuation

3.7

Since the starting of ear molding, participants will be seen once a week by the responding health professional to check and assure the mold is in the right place. Any adverse events will be treated and medical advices will be given accordingly, including suspension or discontinuation of ear molding. Other treatments of CAD received by the participants will be asked and recorded in the case record form (CRF) at each point of follow up. Vouchers will be offered to participants who complete follow up.

Participants can withdraw from the trial on any reason, which will not affect their treatments or usual care. In addition, patients who withdraw due to adverse events will be treated and monitored until recovery.

### Outcome measures

3.8

#### Primary outcome

3.8.1

*Physician assessed improvement.* Two doctors who do are unaware of the group assignment of participants will assess the improvement of auricular form independently. Standardized photographs of participants’ ears will be obtained and assessed using the West China-Peking Union (WPU) index for CAD designed by the research team for the study (see supplementary Table 1 and supplementary Figure 1). Standardized photographs of ears will be obtained by the following way:

(1)Photographs will be obtained at the following anatomical position: upright (showing binaural), fully lateral (showing monaural), lateral 45 degrees (showing monoaural), posterior (showing binaural), and axial position (showing binaural) Among them, the full lateral position and the lateral 45-degree position are about 25 cm from the ear surface;(2)both ears will be photographed in the lateral position and the lateral 45-degree position to facilitate the comparison of the auricle shape;(3)Photographs should clearly and fully show the shape of the auricle, multiple photographs at one angle (1–3 photographs) can be taken for this purpose.

The average score of the 2 physicians’ assessment will be used to calculate the improvement value using the following formula: Improvement value = (total follow-up score — total baseline score) / total baseline score.

The effect size of the improvement value of 0.1 or less will be defined as ineffective, 0.1 to 0.3 as small, 0.3 to 0.5 as medium, and >0.5 as significant. Ineffective and small effect will be classified as nonsignificant improvement (0), and medium or significant effect will be classified as significant improvement (1), turning the effect size into a dichotomous variable, upon which the improvement rate will be calculated.

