#### Secondary outcomes

3.8.2

*WPU CAD index score.* Two physicians will evaluate ear abnormality of participants using the CAD index to obtain a total score, ranges from 0 to 100 from the worst to the best. The final score will be the average of the two physicians’ assessment score.

*Parents’ evaluation of improvement.* Parents of participants will use a visual analogue scale to evaluate the ear abnormality of participants, where 0 represents no improvement and 10 represents complete recovery to normal.

*Anxiety and depression of parents.* The hospital anxiety and depression scale (HADS) will used to evaluate the parents’ anxiety and depression.^[24,25]^

*Quality of life of parents.* The self-administered 12-Item Short Form will be used to assess the quality of life of parents.^[26]^

*Adverse events.* Any adverse events will be recorded in the CRF including but not limited to: skin swelling, skin lesions, allergies, eczema, local infections, necrosis, recurrence, or other unforeseen mild or severe adverse events.

*Time of measurement.* The primary and secondary outcomes, together with any adverse event will be measured and recorded in the CRF at 3 and 12 weeks after the treatment.

*Cost.* The costs will be collected from society perspective, which includes both direct and indirect costs.^[27]^ Direct medical costs will include:

(1)outpatient and inpatient costs: orthosis costs, treatment costs, and examination costs. Since the wearing time limit of each brace is 2 weeks, and there is a possibility of rewearing due to relapse, the number of braces used during one ear treatment can exceed 2, thus the number of braces used will be recorded.(2)The cost of managing complications and adverse reactions.

Indirect medical costs will include: costs incurred by inviting the person to take care of the patient, time lost for family members to take care of the patient, as well as transportation to and from the hospital. Cost-effectiveness analysis will be conducted for the primary outcome physician assessed improvement.

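### The primary improvement value divides by the baseline score on a worst-to-best index, so an ear starting above 76.9 cannot count as a responder even if it becomes fully normal

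*Protocol article*

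**What the plan says.** Under Primary outcome (3.8.1), two blinded physicians rate standardised photographs, "assessed using the West China-Peking Union (WPU) index for CAD designed by the research team for the study". Their average score enters the formula "Improvement value = (total follow-up score — total baseline score) / total baseline score". The result is graded: "0.1 or less will be defined as ineffective, 0.1 to 0.3 as small, 0.3 to 0.5 as medium, and >0.5 as significant". It is then dichotomised. Ineffective and small count as 0, while "medium or significant effect will be classified as significant improvement (1"), so the responder cut lies at 0.3. The improvement rate is built on this variable.

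Under Secondary outcomes (3.8.2), the same index has a "total score, ranges from 0 to 100 from the worst to the best". That section also bases the cost-effectiveness analysis on the primary outcome.

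The inclusion criteria (3.2.1) list many deformities, ending with "mixed ear deformities combining 2 or more deformities, and other auricle distortions", and add grade I microtia. Neither they nor the exclusion criteria (3.2.2) state a minimum severity or a limit on the baseline score.

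The Sample size section (3.10) plans for 90% against 70%, alpha 0.05 and power 0.9, giving 79 evaluable infants per group.

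**The concern.** On a scale where 100 is a normal ear, relative change from baseline measures the gain against what was already normal. A mildly affected ear has a large denominator and little room to gain. A severely affected ear has a small denominator and much room. The formula can therefore grade complete correction of a mild ear as small or even ineffective, and a gain of a few points in a severe ear as a response.

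Two things are at stake. The first is meaning: the same responder label stands for different degrees of correction in different infants, and the cost-effectiveness ratio inherits this. The second is power: infants who cannot respond in either arm lower both rates and shrink the difference the trial was sized to detect.

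**Working it through.** **Inputs.** Formula and cut-offs: Primary outcome. Scale range and direction: Secondary outcomes. Rates, alpha, power and 79 per group: Sample size. The share f of infants with baseline above 76.9 is not in the document and is assumed over a range.

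**The plan's own figure.** Two proportions, unpooled variance, two-sided 0.05, power 0.90:

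n = (1.960 + 1.282)² × (0.9×0.1 + 0.7×0.3) / 0.2² = 78.8, rounded up to 79. The stated figure reproduces.

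**Ceiling.** With full normalisation to 100, the value is (100 − B)/B. It falls to a threshold t at B = 100/(1 + t):

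- t = 0.3: 100/1.3 = 76.9. Above this no infant can be a responder.
- t = 0.5: 100/1.5 = 66.7. Above this the top category is out of reach.
- t = 0.1: 100/1.1 = 90.9. At or above this, full normalisation is graded ineffective.

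Examples: 80 to 100 gives 20/80 = 0.25 (non-responder); 90 to 100 gives 10/90 = 0.11 (non-responder). At B = 0 the value is undefined.

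**Gain needed to respond.** This is 0.3B points, or 0.3B/(100 − B) of the deficit:

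| Baseline | Points needed | Share of deficit |
|---|---|---|
| 10 | 3 | 3.3% |
| 20 | 6 | 7.5% |
| 50 | 15 | 30% |
| 70 | 21 | 70% |
| 75 | 22.5 | 90% |
| 80 | 24 (only 20 available) | 120% |

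**Effect on power.** Assume the 90% and 70% apply to infants at or below 76.9 and that the rest are forced non-responders. The rates become 0.9(1 − f) and 0.7(1 − f). Power at 79 per arm is Φ(difference/SE − 1.96), where SE = √{[p₁(1 − p₁) + p₂(1 − p₂)]/79}. For f = 10%: SE = √(0.387/79) = 0.070; 0.18/0.070 = 2.57; Φ(0.61) = 73%.

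| f | Rates | Power | n per arm for 90% power |
|---|---|---|---|
| 0 | 90% v 70% | 90% | 79 |
| 3.6% | 86.8% v 67.5% | 84% | – |
| 10% | 81% v 63% | 73% | 126 |
| 20% | 72% v 56% | 57% | 184 |
| 30% | 63% v 49% | 43% | 259 |

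To show how far f could range, take baselines that are Normal and truncated to 0–100, again purely as an assumption. Mean 40, SD 15 gives f = 0.7% and power 89%. Mean 50, SD 15 gives 3.6% and 84%. Mean 60, SD 15 gives 13% and 68%. Mean 70, SD 12 gives 28% and 46%.

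**Is 90% attainable?** If every treated ear were normalised, the highest possible rate is 1 − f. It falls below 90% only when f exceeds 10%.

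**The case against.** The strongest reply is that the size of the effect rests on material not shown. The scoring is in a supplementary table. An index built for these deformities might place nearly every eligible ear well below 76.9, and then little power is lost. This stands: the absence of a severity floor shows that mild ears may enter, not that they will score above 77. The low-baseline examples are equally unverified. The power model also leaves out that low-baseline ears pass easily, which could raise both rates.

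A reader might infer that the planned 90% against 70% is unattainable. The document does not support that, since 90% is excluded only if f exceeds 10%. A reader might also infer that any chance imbalance in severity passes straight into the result. Randomisation protects against systematic imbalance, and the Statistical analysis section plans a model adjusted for individual and hospital factors, although it does not name the baseline score.

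The mean difference in index score is analysed as a secondary outcome, so full correction of mild ears is not lost from the results altogether.

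On the cut itself, "0.1 to 0.3 as small, 0.3 to 0.5 as medium, and >0.5 as significant" puts exactly 0.3 in two categories. The end categories suggest that an upper limit belongs to the lower class, so this is loose wording rather than a substantive flaw.

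Reading the scale the other way round does not rescue the formula: it contradicts the stated direction, and improving ears would then score negative.

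**Conclusion.** The concern holds as a defect in the definition of the primary outcome. The ceiling follows exactly from the stated formula and scale and needs no assumption: above 76.9 a fully normalised ear is a non-responder, and at 90.9 or higher it is graded ineffective. The varying meaning of response, from 3.3% of the deficit at baseline 10 to 70% at baseline 70, is equally exact.

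The practical size is unknown. Power at 79 per arm runs from about 90% with no infants above 76.9 to 43% with 30% above, given that the planning rates apply to the remainder. Those rates come from the literature, and the document does not show that they were measured by a 0.3 relative-change rule. The harm is loss of interpretability and possible dilution in both arms, not bias towards either.

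**What to change.** Define the improvement value as the share of the baseline deficit corrected, (follow-up − baseline)/(100 − baseline). It equals 1 for full normalisation from any baseline below 100, is defined at 0, and uses scores already collected.

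Before any follow-up data are seen, justify a responder cut on this scale and write it as a single inequality. Carrying 0.30 over unchanged will not do: at baseline 95 it would need only 0.3 × 5 = 1.5 points. The cut should be set so that gains within rater error in mild ears do not count.

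Name the baseline index score among the individual-level covariates of the primary model.

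The cost is a protocol amendment with no new data collection. The 0.1/0.3/0.5 labels and the 90% and 70% planning rates must be re-confirmed on the new scale, and the sample size with them. Near-normal baselines become the end most sensitive to rating noise.

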#### Secondary outcomes

3.8.2

*WPU CAD index score.* Two physicians will evaluate ear abnormality of participants using the CAD index to obtain a total score, ranges from 0 to 100 from the worst to the best. The final score will be the average of the two physicians’ assessment score.

*Parents’ evaluation of improvement.* Parents of participants will use a visual analogue scale to evaluate the ear abnormality of participants, where 0 represents no improvement and 10 represents complete recovery to normal.

*Anxiety and depression of parents.* The hospital anxiety and depression scale (HADS) will used to evaluate the parents’ anxiety and depression.^[24,25]^

*Quality of life of parents.* The self-administered 12-Item Short Form will be used to assess the quality of life of parents.^[26]^

*Adverse events.* Any adverse events will be recorded in the CRF including but not limited to: skin swelling, skin lesions, allergies, eczema, local infections, necrosis, recurrence, or other unforeseen mild or severe adverse events.

*Time of measurement.* The primary and secondary outcomes, together with any adverse event will be measured and recorded in the CRF at 3 and 12 weeks after the treatment.

*Cost.* The costs will be collected from society perspective, which includes both direct and indirect costs.^[27]^ Direct medical costs will include:

(1)outpatient and inpatient costs: orthosis costs, treatment costs, and examination costs. Since the wearing time limit of each brace is 2 weeks, and there is a possibility of rewearing due to relapse, the number of braces used during one ear treatment can exceed 2, thus the number of braces used will be recorded.(2)The cost of managing complications and adverse reactions.

Indirect medical costs will include: costs incurred by inviting the person to take care of the patient, time lost for family members to take care of the patient, as well as transportation to and from the hospital. Cost-effectiveness analysis will be conducted for the primary outcome physician assessed improvement.

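### The primary outcome is measured at two times with neither designated, and the later one falls after stated follow-up ends and controls may have been molded

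*Protocol article*

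**What the plan says.** All references are to the protocol article.

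- **Section 3.8.2, Time of measurement.** "The primary and secondary outcomes, together with any adverse event will be measured", and the times given are "measured and recorded in the CRF at 3 and 12 weeks after the treatment". The two times have equal standing.
- **Section 3.5, Intervention.** Molding begins within 3 days of birth, "with a treatment duration of 2 weeks and followed up until 6 weeks from the start of the treatment".
- **Section 3.6, Control.** "Participants will be followed up at the same intervals as the intervention group until the sixth week after birth". Then: "After that, participants will be offered ear molding treatment as the same as the intervention group". The offer depends on the parents' wishes and applies only "if the participant is not recovered spontaneously".
- **Section 3.8.1, Primary outcome.** "Improvement value = (total follow-up score — total baseline score) / total baseline score". The follow-up score in this formula carries no date.
- **Sections 3.10 and 3.12.** Neither the sample-size rates (90% and 70%) nor the primary risk ratio is tied to a time point. The effectiveness analysis is by intent to treat, with one significance level of 0.05.

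**The concern.** Three problems meet here.

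1. **The schedules contradict each other.** One section measures the primary outcome at a time when two others say follow-up has ended.
2. **The later comparison answers a different question.** Section 3.1 sets molding against a waiting list. Once controls have been offered molding, an intent-to-treat analysis still counts the treated ones as controls. The contrast becomes immediate versus optional deferred molding, and successful late molding pulls it towards no difference.
3. **No time point decides the trial.** With two candidate primary times, the choice could be made after the results are seen. The phrase that dates both times from the treatment also has no meaning for controls, who have had none by week 6.

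The cost-effectiveness analysis uses the same primary outcome, so it inherits the ambiguity. Section 3.8.2 states no window for collecting costs.

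**Working it through.** **Step 1: calendar, counted from the start of treatment.** Section 3.5 gives a 2-week course.

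| Assessment | Counted from end of course | Counted from start of course |
|---|---|---|
| 3 weeks | 2 + 3 = week 5 | week 3 |
| 12 weeks | 2 + 12 = week 14 | week 12 |
| Stated end of follow-up | week 6 | week 6 |

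Controls are followed to week 6 after birth. Because molding starts within 3 days of birth, the two arms' end dates differ by days only. On either count the earlier assessment falls before the offer to controls, and the later one falls 6 to 8 weeks after it.

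**Step 2: reproduce the protocol's sample size.** Inputs from section 3.10: 0.90 versus 0.70, alpha 0.05, power 0.90. Sidedness is not stated, so two-sided is assumed. With unpooled variance:

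n = (1.960 + 1.282)² × (0.90 × 0.10 + 0.70 × 0.30) / 0.20² = 10.507 × 0.30 / 0.04 = 78.8, so 79 per group.

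This matches the stated 79. At 79 per group the same formula gives power 90%.

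**Step 3: dilution at 12 weeks.** Let c be the share of the 30% unrecovered controls who take up molding, and q the share of those in whom it succeeds. The documents give neither, so both are assumptions shown over a range. Using 70% as the spontaneous rate at this time is also an assumption.

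Control rate p = 0.70 + 0.30 × c × q

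Power = Φ(d − 1.960) + Φ(−d − 1.960), where d = (0.90 − p) / √[(0.09 + p(1 − p)) / 79]

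| Uptake c | p at q = 0.5 | Power | p at q = 0.9 | Power |
|---|---|---|---|---|
| 0 | 0.700 | 90% | 0.700 | 90% |
| 10% | 0.715 | 86% | 0.727 | 82% |
| 25% | 0.738 | 77% | 0.768 | 62% |
| 50% | 0.775 | 58% | 0.835 | 23% |
| 75% | 0.813 | 35% | 0.903 | 5% |

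Worked example for c = 0.5, q = 0.9: p = 0.70 + 0.135 = 0.835; standard error = √[(0.09 + 0.1378) / 79] = 0.0537; d = 0.065 / 0.0537 = 1.21; power 23%. In the bottom right cell the control rate has reached the intervention rate, and 5% is simply the test level.

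**Step 4: multiplicity, conditional only.** If each time were tested separately at 0.05, the familywise error would be 1 − 0.95² = 9.75% for independent tests, and about 7.8% at a correlation of 0.8 (bivariate normal).

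**The case against.** **The protocol does not say that both times are tested at 0.05.** A reader might infer it from two primary times and one significance level. But section 3.12 describes one risk ratio from a multi-level model, and a repeated-measures model with a single treatment effect would fit that wording. Multiplicity rules are also commonly left to a statistical analysis plan, which is not shown. This stands: the 7.8% to 9.75% is conditional and is not an error rate of the plan as written.

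**The large power losses rest on favourable late results.** Section 3.10 ties the 90% rate to correction within 2 weeks of age, and the Introduction says that earlier intervention does better. Deferred molding starts after week 6, so q = 0.9 is the optimistic end. At 50% uptake with 30% success, p = 0.745 and power is 74%. The Introduction also places 70% natural recovery at 1 year of age, so the true base rate at week 12 to 14 may differ in either direction. This stands, which is why the result is given as a range.

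**Not every unrecovered control is treated.** The offer depends on the parents. This also stands: contamination follows uptake.

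**A 12-week cost window is not stated.** A reader might infer that the control arm will be charged for late molding. The measurement-time sentence names the outcomes and adverse events; the cost paragraph after it gives no window. Charging late molding to controls would in any case be proper accounting if the comparison were labelled immediate versus deferred.

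**Table 1 is not visible and may list the visits.** It limits certainty about the intended schedule, but it cannot remove the contradiction in the text.

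None of this answers the central point. An analysis plan could choose a time point, but it cannot place week 12 or 14 inside a 6-week follow-up or restore an untreated control group after the offer.

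**Conclusion.** The point holds in this form. The text contradicts itself on follow-up length. It designates no primary time point, and it places one of two candidate primary assessments after controls may have received the intervention. Under the stated intent-to-treat analysis, the 12-week contrast no longer estimates molding versus waiting list.

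The size cannot be fixed from the documents. Under the assumptions above, power at 12 weeks is little changed at 10% uptake (86% to 82%), materially reduced at 25% (77% to 62%), and poor at 50% or more (58% to 23%, then 35% to 5%).

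It would go too far to conclude that the trial as a whole is contaminated. The earlier assessment precedes the offer to controls and keeps the planned comparison, at least for a single 2-week course. Because a sound primary time point is already scheduled and is simply not named, this should be corrected before analysis.

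**What to change.** 1. **Designate one primary time point before controls are offered molding**, and test only that at 0.05. Use the existing earlier assessment, dated from randomisation or birth in both arms, for example about week 5 and no later than week 6. A date counted from the end of treatment will not do. Controls have no course, and section 3.8.2 allows rewearing after relapse: two 2-week braces in succession would put the assessment at 4 + 3 = week 7, past the offer.
2. **Keep the 12-week assessment as secondary**, labelled immediate versus deferred molding. It remains useful for recurrence, so it should not be dropped.
3. **Reconcile sections 3.5 and 3.6 with section 3.8.2** on the length of follow-up. This asks for consistency and takes no position on when controls should be treated.
4. **State the cost window and match it to the comparison.** Use the period before the offer for molding versus waiting list. Use the longer period only if the analysis is labelled immediate versus deferred.

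This needs wording only, with no extra visits or participants. The price is that the 12-week result loses primary status, and that a cost window closing before the offer leaves out later relapse and rewearing costs.

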### Sample size

3.10

The test level α is 0.05, and the statistical power is (1- β) is 0.9. According to literature reports, the effective rate of ear mold correction within 2 weeks of age was about 90%, and the natural improvement rate without intervention was about 70%. The sample content was calculated to be 79 cases per group. According to the possible loss of follow-up of 20%, the sample was expanded to 95 cases in each group, with a total of 190 cases in both groups.

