### Statistical analysis

3.12

For descriptive analysis, mean and standard deviation will be used for symmetric continuous variables, while median, first quartile, and third quartile will be used for asymmetric continuous variables. Frequency and percentage will be used to describe categorical variables. In baseline analysis of comparability between groups, analysis of variance will be used for continuous variables and Chi square test will be used for categorical variables.

The primary outcome improvement rate will be compared between groups and risk ratio with 95% confidence interval will be estimated using multi-level modelling adjusting for individual and hospital level factors. For secondary outcomes, mean difference with 95% confidence interval of WP CAD index score, parents’ evaluation of improvement (visual analogue scale), anxiety and depression, quality of life using multi-level modelling. Potential confounding factors at individual and study site level, and secular trend will be included/adjusted in the models. Intent to treat analysis will be conducted for the effectiveness analysis. Sensitivity analysis will be carried out using per protocol analysis. The significant level will be at 0.05. Statistical analysis will be performed using Stata 15.0 SE and MLN.

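### The 12-week assessment of the primary outcome falls after the stated 6-week follow-up and after controls are offered molding, and the text does not say which visit is primary

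*Protocol article*

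**What the plan says.** The protocol article gives two timetables.

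- Section 3.8.2 (Time of measurement) has the primary and secondary outcomes, with adverse events, "recorded in the CRF at 3 and 12 weeks after the treatment".
- Section 3.5 describes the intervention arm as starting molding within 3 days of birth, "with a treatment duration of 2 weeks and followed up until 6 weeks from the start of the treatment".
- Section 3.6 says of controls: "Participants will be followed up at the same intervals as the intervention group until the sixth week after birth". Once that period is over, "participants will be offered ear molding treatment as the same as the intervention group", if the parents wish it and the ear has not recovered on its own.

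Section 3.12 adds: "Intent to treat analysis will be conducted for the effectiveness analysis", and "Sensitivity analysis will be carried out using per protocol analysis". The outcome definition (3.8.1), the sample size (3.10) and the analysis (3.12) each work with a single improvement rate, and none of them attaches it to a visit.

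**The concern.** Follow-up that stops at week 6 cannot contain an assessment at week 12. The gap matters because the control arm changes at week 6. Before then it is an untreated waiting list. Afterwards it is a mixture of infants who recovered unaided, infants molded late, and infants never molded. Molding is offered only to controls who have not recovered, so each successful late course turns a control failure into a control success.

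The two visits therefore answer different questions. If the 12-week visit were taken as primary, which the text allows, the trial would understate the effect of molding against no treatment. The cost-effectiveness analysis would be affected too, because section 3.8.2 bases it on the same outcome. With the visits unranked, the choice between them could decide the trial.

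The clock is also undefined. The text does not say whether it runs from the start or the end of molding. Controls have no treatment before week 6 from which to count.

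**Working it through.** **1. Where the visits fall.** Inputs: molding starts within 3 days of birth and lasts 2 weeks (3.5); visits at 3 and 12 weeks (3.8.2); follow-up to week 6 (3.5, 3.6).

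| Clock | First visit | Second visit | Second visit beyond week 6 |
|---|---|---|---|
| From start of molding | week 3 | week 12 | 12 − 6 = 6 weeks |
| From end of a 2-week course | 2 + 3 = week 5 | 2 + 12 = week 14 | 14 − 6 = 8 weeks |

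For a single 2-week course, the first visit precedes the week-6 offer on both clocks, and the second lies outside stated follow-up on both. A control who accepts at week 6 finishes a 2-week course at 6 + 2 = week 8, before the second visit.

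**2. What the analysis sets do.** Intention to treat keeps late-molded controls in the control arm, so the 12-week contrast is immediate versus optional deferred molding. The per-protocol sensitivity analysis need not remove them, because accepting the offer follows the protocol.

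**3. The plan's own sample size.** Inputs from 3.10: 90% versus 70%, α 0.05 (taken as two-sided), power 0.90. With unpooled variance:

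n = (1.960 + 1.282)² × (0.9 × 0.1 + 0.7 × 0.3) / 0.2² = 78.8, so 79 per arm.

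This reproduces the stated figure. Its control rate is an untreated one: "the natural improvement rate without intervention was about 70" per cent.

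**4. What crossover could do at 12 weeks (illustration).** Assume 90% versus 70% untreated holds at 12 weeks and 79 per arm are analysed. Control rate after crossover = 0.70 + 0.30 × (uptake × success among unrecovered controls). Power uses the two-sided normal approximation with pooled variance under the null:

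power = Φ{[d − 1.960 × √(2 p̄(1 − p̄)/n)] / √[(p₁(1 − p₁) + p₂(1 − p₂))/n]}

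Here p₁ and p₂ are the molding and control rates, p̄ is their mean and d their difference. For 90% versus 70%: (0.2 − 1.960 × 0.0636) / 0.0616 = 1.22, and Φ(1.22) = 0.889. The other rows follow in the same way.

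| Control rate | Uptake × success needed | Difference | Risk ratio | Power |
|---|---|---|---|---|
| 70% | 0 | 20 points | 0.90/0.70 = 1.29 | 0.889 |
| 75% | 0.05/0.30 = 0.17 | 15 points | 0.90/0.75 = 1.20 | 0.702 |
| 80% | 0.10/0.30 = 0.33 | 10 points | 0.90/0.80 = 1.13 | 0.420 |
| 85% | 0.15/0.30 = 0.50 | 5 points | 0.90/0.85 = 1.06 | 0.156 |

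**5. Counter-case.** The Introduction ties the 70% to a later age: "about 70% infants with CAD at birth will recover naturally at 1 years old". The untreated rate at 12 weeks may therefore be lower. Suppose it is 50% and crossover raises controls to 70% (uptake × success = 0.20/0.50 = 0.40). The difference halves from 40 to 20 points, while power goes from above 0.999 to 0.889. Power is then adequate, but the estimate still does not describe molding versus no treatment.

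**The case against.** The strongest reply is that only week 6 against week 12 is a true contradiction. Offering treatment to controls after a waiting period is ordinary waiting-list design and is openly stated. A later intention-to-treat comparison of immediate with deferred molding is legitimate, and the first visit already supplies an untreated comparison. The visit schedule (Table 1) is not shown, and the full protocol or an analysis plan might rank the visits. Section 3.7 has other treatments recorded at each follow-up, so late molding in controls can be counted. The control rates of 75% to 85% are chosen, not derived.

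Much of this stands as a limit on the finding:

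- The absence of a primary visit can be claimed only for the visible text.
- The power figures are illustrative.
- The offer at week 6 should stay.
- Recording other treatments makes the remedy easier, though it does not say how molded controls are analysed.
- Section 3.8.2 allows more than two braces of 2 weeks each. With two worn in sequence, an end-of-treatment clock would put the first visit at 4 + 3 = week 7, after the offer. This is a further reason to fix a common age.

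The conflict itself is untouched. Table 1 could define the clock, but it cannot make 6-week follow-up contain a 12-week assessment. If week 6 was meant to close only the controlled phase, the 12-week visit comes after crossover by design and should not share unranked status with the first.

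**Conclusion.** The concern holds and should be fixed. On either clock, the second assessment lies 6 to 8 weeks beyond stated follow-up and after controls may have been molded. An intention-to-treat result at that visit estimates immediate versus deferred molding, diluted towards no difference to the extent that late molding succeeds.

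The size of the dilution cannot be computed from the document, because uptake, late success and the untreated rate at 12 weeks are not given. If the planning rates hold at 12 weeks, a rise of 5 to 10 points in controls removes a quarter to a half of the planned difference. If the untreated rate is lower, power may survive but the estimate still changes meaning.

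The trial is not compromised beyond repair. The first visit, held at a fixed age before week 6, gives the comparison the trial sets out to make, provided that choice is committed to in advance.

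**What to change.** 1. Anchor outcome visits in both arms to birth or randomisation, not to treatment.
2. Name the first assessment as primary, at one common age before the week-6 offer and regardless of any brace extension: about week 3 if the clock was meant to start with molding, about week 5 if with its end.
3. Keep the 12-week visit as secondary, at one fixed age in both arms, labelled immediate versus deferred molding. Report how many controls had been molded by then.
4. Extend the follow-up stated in sections 3.5 and 3.6 to cover that visit.
5. State which visit the cost-effectiveness analysis uses.

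The cost is wording in the protocol and the CRF; both visits and the week-6 offer remain. There are three downsides. A few infants with re-worn braces may still be in treatment at the primary visit. A week-3 visit comes only about 1 week after a 2-week course ends, so later relapse would show only at 12 weeks; a week-5 visit allows about 3 weeks. The 70% control rate should also be checked against the chosen age, since the Introduction attaches that figure to 1 year.
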